### Metabolic parameters

Fasting blood glucose is measured in capillary blood using Breeze®2 glucose meters (Bayer Health Care LLC, Basel, Switzerland). An oral glucose tolerance test is performed in a subset of the study population according to the WHO protocol [47,48]. Glucose levels are measured in capillary blood using Breeze®2 glucose meters after overnight fasting and 2 hours after ingesting 75 g of anhydrous glucose dissolved in 200 cc of water. Insulin, HbA1c and lipid profiles will be measured in an internationally accredited laboratory. HOMA-IR, a well-validated measure of insulin resistance will be calculated to estimate insulin resistance [49].

### Immunological methods

The immunological parameters that will be studied are 1) Total IgE levels as one of the markers of a Th2 response and its relation to metabolic parameters, 2) Circulating pro- and anti-inflammatory cytokines in order to study their relationship to metabolic parameters, 3) Antigen specific IgE and IgG to *Ascaris lumbricoides* to monitor antibody responses to one of the helminths studied as a marker of changing immune responses as a result of anthelmintic treatment, 4) Granulocyte (neutrophil and eosinophil) frequencies and their activation to assess whether granulocytes, in particular eosinophils which are associated with Th2 response, are linked to helminth infections and metabolic parameters, 5) Peripheral blood mononuclear cells (PBMC) subset analysis and polarisation by flow cytometry in order to assess the relationship between immune cell frequencies (T cell subsets, B cell subsets, monocyte subsets, NK cells and myeloid suppressor cells) in situ as well as after activation and metabolic parameters.

#### Total IgE

Total IgE will be measured using ELISA with rabbit anti-human IgE antibodies (Dako, Glostrup, Denmark) and goat anti-human IgE biotinylated antibodies (Vector Laboratories, Burlingame, CA, USA) as capture and detection antibodies, as described previously [43]. The World Health Organization standard of human serum IgE was used as a reference (National Institute for Biological Standards and Control). The results will be expressed in International Units (IU).

#### Circulating cytokines

Pro and anti-inflammatory cytokines (TNFα, IFNγ, IL-1, IL-6, IL-10, TGFβ) will be measured in serum samples using cytokine kits with high sensitivity.

#### Ascaris-specific IgE

*Ascaris* antigen will be prepared from *Ascaris lumbricoides* worms as described previously [50]. Maxisorp plates (Thermo Fisher Scientific, Roskilde, Denmark) will be coated overnight with 5 μg/ml *Ascaris* antigen in 0.1 M carbonate buffer (pH 9.6). Plates will be blocked for 1 hour with PBS containing 2% bovine serum albumin. Samples will be diluted 1/60 in 0.1 M Tris–HCl containing 0.05% Tween-20 and incubated overnight together with a pool of positive standard plasma containing 1 × 10^6^ arbitrary units (AU) parasite specific IgE. After a washing step, goat anti-human IgE biotinylated antibodies (Vector) will be incubated followed by streptavidin-HRP (Sanquin, Amsterdam, the Netherlands). The color is developed by adding 3,3′,5,5′ tetramethylbenzidine (TMB) (KPL, Gaithersburg, MD, USA). The reaction will be stopped by adding 1.8 M H_2_SO_4_ and absorbance will be read at 450 nm in an automated plate reader.

#### Ascaris-specific IgG isotypes

Maxisorp plates will be coated with *Ascaris* antigen as described for *Ascaris* specific IgE above. Blocking will be done using PBS containing 5% bovine serum albumin. Samples will be diluted 1/1000, 1/10, 1/5 or 1/25 for IgG1, IgG2, IgG3 and IgG4 respectively, and a pool of positive standard plasma containing 1 × 10^6^ arbitrary units (AU) parasite specific IgG isotypes will be included in each plate. After overnight incubation, HRP-labelled anti human IgG isotypes (Sanquin) in PBS 0.05% Tween-20 will be added for 4 hours incubation at 37°C using the following dilutions: 1/3000 for anti IgG1 (HP6188) and anti IgG4 (HP6196); 1/1000 for anti IgG2 (HP6014) and anti IgG3 (HP6095). TMB substrate will be used to develop the color and the reaction will be stopped as described above.

#### Whole blood stimulation and fixed granulocyte cryopreservation

To study the expression of activation markers on granulocytes, 600 μl of heparinised venous blood is divided over 3 polystyrene tubes (200 μl/tube). After a pre-incubation of 5 minutes in a 37°C waterbath, a 5 minutes stimulation at 37°C is performed with N-Formyl-Met-Leu-Phe (FMLP, 10^−5^ M; Sigma, Saint Louis, MO, USA) or eotaxin (10^−7^ M; R&D systems, Abingdon, UK). Subsequently, 4 ml of FACS lysing solution (BD) is added and after an incubation period of 15 minutes at room temperature the red blood cells is lysed while white blood cells, including granulocytes, become fixed. Cells are washed with RPMI 1640 containing 10% heat-inactivated FCS and then resuspended in RPMI 1640 containing 10% of heat-inactivated foetal calf serum (FCS) and 10% dimethyl sulfoxyde (DMSO). Cryovials containing the cell suspension are placed at −80°C for minimum of 4 hours, followed by storage in liquid nitrogen until analysis.

#### PBMC cryopreservation

Peripheral blood mononuclear cells (PBMCs) are isolated from heparinised venous blood using Ficoll density gradient centrifugation within 12 hours after blood collection. After isolation, cells are cryopreserved in RPMI 1640 containing 20% of heat-inactivated foetal calf serum (FCS) and 10% dimethyl sulfoxyde (DMSO). Cryovials containing the cell suspension are transferred to a freezing unit which is placed in a −80°C freezer for minimum of 4 hours. Subsequently, vials are stored in liquid nitrogen until analysis.

### Metabolomics for metabolic profiling

Urine samples and blood samples from heparinized blood are kept at −20°C at the FCRC and subsequently stored at −80°C at the University's laboratory for future metabolomics measurements. The exploratory metabolomics analysis will be performed by 1H-NMR and LC-MS metabolomics, a combination of NMR and LC-MS proposed for this study provides a comprehensive coverage of metabolome and as such increase the probability of finding physiologically meaningful associations within the data.

### Data management and statistical analyses

A centrally accessible database designed in Microsoft Access is established and the data is entered by well-trained data entry personnel. Descriptive data will be summarized for continuous variables as mean +/− SD for normally distributed data and median (range) for non-normally distributed data. Categorical data will be expressed as proportions.

The effect of anthelmintic treatment on insulin resistance (HOMA-IR) as our primary outcome will be assessed using an intention to treat approach after 1 year of treatment using mixed models to account for the correlation within households, in which relevant confounders (including age, gender, BMI, village) are entered. The characterization of immune responses to helminth infections and systemic inflammation will be assessed by measuring cytokine profiles. Moreover, for these analyses multilevel modelling will be used and the use of longitudinal data will take repeated measurement into account [51]. The mediation of helminth’s effects on insulin resistance via immune responses will also be assessed.

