### Outcomes

As this study aims to assess the effect of anthelmintic treatment on whole-body insulin sensitivity, our primary outcome is a change in insulin resistance as assessed by HOMA-IR between both treatment arms after one year of treatment. Secondary outcomes are changes in body mass index and waist circumference, fasting blood glucose, 2 h-glucose levels after oral glucose tolerance test, HbA1c, serum lipid levels, immunological parameters, and efficacy of anthelmintic treatment.

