### Sample size

Sample size is calculated according to intention to treat analysis in which we will need 1580 subjects in total. Based on our previous study [45] we assume that the average household size is 4 and that around 20% will be lost to follow up after one year. We use a significance level of 5% and a power of 80%. Correlations within households are taken into account by using the correction factor 1 + (m-1) ICC, with m being the household size and ICC the intra-class correlation. The sample size is computed for a difference in mean between the two treatment groups of 0.18 and an ICC of 0.1.

For the subgroup of individuals undergoing an oral glucose tolerance test, a sample size of 335 subjects in total is calculated assuming that around 20% will be lost to follow up after one year and using a significance level of 5% and a power of 80%. The sample size is computed for a difference in mean of 10.3 mg/dL and a standard deviation of glucose level of 30 mg/dL.

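### The primary outcome is worded as a change in HOMA-IR, but the stated model analyses HOMA-IR after one year and does not name baseline HOMA-IR as a covariate, which gives up precision that costs nothing to keep

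*Protocol article*

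**What the plan says.** In the protocol article, under Outcomes: "our primary outcome is a change in insulin resistance as assessed by HOMA-IR between both treatment arms after one year of treatment". The Abstract likewise speaks of changes in insulin resistance.

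Under Data management and statistical analyses, HOMA-IR is to be assessed by intention to treat after one year of treatment, "using mixed models to account for the correlation within households, in which relevant confounders (including age, gender, BMI, village) are entered". The text does not say whether the dependent variable is the one-year value or the change from baseline, and baseline HOMA-IR is not named. After a sentence on cytokine profiles comes: "for these analyses multilevel modelling will be used and the use of longitudinal data will take repeated measurement into account".

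Under Sample size: "Sample size is calculated according to intention to treat analysis in which we will need 1580 subjects in total", and "The sample size is computed for a difference in mean between the two treatment groups of 0.18 and an ICC of 0.1". No SD is given for HOMA-IR. The text does not say whether the difference of 0.18 is between one-year means or mean changes.

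Under Sample collection and in Table 1, examined participants give fasting blood at baseline and at one year, and metabolic parameters are scheduled at both visits.

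**The concern.** Three sections describe the primary comparison and do not settle on one quantity. The outcome is worded as a change, the model as HOMA-IR after one year, and the sample size as a difference in means without a time point.

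The choice matters because the candidate analyses differ in precision:

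- a one-year comparison that ignores baseline discards information already collected;
- an unadjusted change score uses baseline, but with a fixed weight of one, which adds noise when the two measurements correlate weakly;
- adjusting for baseline as a covariate is at least as precise as either, for any rho between 0 and 1.

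At stake are the width of the primary confidence interval and the handling of a chance baseline difference between arms formed from households. Bias is not at issue, since randomisation protects against systematic imbalance.

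**Working it through.** **Inputs from the article (Sample size):** total 1580; 5% significance and 80% power; difference 0.18; ICC 0.1; household size 4; 20% loss; correction factor 1 + (m-1) ICC.

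**Assumed, because not stated:** two-sided test; 1:1 allocation; an SD on the same scale as 0.18; the same design effect for every model; the correlation rho.

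**Step 1. Check the formula where the SD is given.** For the glucose tolerance subgroup (difference 10.3 mg/dL, SD 30 mg/dL), the two-sided normal formula gives 134 per arm, so 268 in total, and 268 / 0.8 = 335. This matches the stated 335 exactly.

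**Step 2. Back-solve the primary SD.** The 1580 cannot be reproduced from stated inputs alone.

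- Design effect: 1 + (4-1) x 0.1 = 1.3.
- Evaluable: 1580 x 0.8 = 1264. Effective number per arm: 1264 / 1.3 / 2 = 486.2.
- SD = 0.18 x sqrt(486.2 / 2) / (1.960 + 0.842) = 1.00.
- In reverse, SD 1.0 needs 485 per arm, and 2 x 485 x 1.3 / 0.8 = 1577 after rounding up, against the stated 1580.

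If loss was instead allowed for by multiplying by 1.2, the implied SD is 1.02.

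**Step 3. Compare the three analyses at N = 1580.** Take the implied SD to be that of a single-time value. The SD is then multiplied by:

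- 1 for the one-year value without baseline;
- sqrt(2(1 - rho)) for the unadjusted change;
- sqrt(1 - rho^2) for the baseline-adjusted one-year value.

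Power = Phi(2.802 / factor - 1.960), where 2.802 is 0.18 divided by the planned standard error.

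| rho (assumed) | One-year, no baseline | Unadjusted change | Baseline-adjusted | N for 80% with adjustment |
|---|---|---|---|---|
| 0.3 | 80.0% | 65.8% | 83.6% | 1438 |
| 0.4 | 80.0% | 72.5% | 86.4% | 1328 |
| 0.5 | 80.0% | 80.0% | 89.9% | 1185 |
| 0.6 | 80.0% | 87.9% | 93.8% | 1012 |

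Example at rho 0.5: factor sqrt(1 - 0.25) = 0.866; 2.802 / 0.866 - 1.960 = 1.275; power 89.9%.

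Relative to the one-year comparison, adjustment is worth 1/(1 - rho^2) in information: 10% more at rho 0.3, 33% at 0.5 and 56% at 0.6.

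**Step 4. Limits of these figures.** They compare adjustment for baseline with no adjustment at all. The stated model already includes age, gender, BMI and village. As far as those explain baseline HOMA-IR, the added gain is smaller. The article gives nothing from which to quantify this.

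**The case against.** A reader might infer from the change wording that the trial falls below its stated 80% power. The article does not support that. A shortfall needs three things together: an unadjusted change score as the analysed variable, a sizing SD that belongs to a single time point, and rho below 0.5. None is stated.

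- The statistical section speaks of HOMA-IR after one year, and that comparison keeps 80% at every rho.
- The outcome sentence can also be read as a between-arm difference at one year.
- If 0.18 and its SD already refer to change, the shortfall disappears.
- Recruitment also exceeded the target. With the 1669 consenting subjects, the same loss and design effect 1.3, the one-year comparison has about 82% power. If all 752 households contributed (an assumption), the mean is 1669 / 752 = 2.2 examined members, the design effect is about 1.12, and power is about 87%.

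It is also tempting to say that baseline HOMA-IR is excluded. The covariate list is introduced as an open one, so it is unnamed rather than ruled out. A condensed article may leave the full covariate set to the analysis plan. This limits the point but does not remove it. The article states a primary model and names covariates, and it selects them as confounders, a criterion that does not naturally lead to the baseline outcome in a randomised trial. The sentence on repeated measurement follows the cytokine analyses and refers back to them, so it does not clearly cover HOMA-IR.

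A third inference would be that a one-year analysis breaks the intention-to-treat claim by dropping the expected 20% lost. That is weak: intention to treat concerns analysis by assigned arm, the sample size already allows for the loss, and missing-data handling is commonly left to the analysis plan.

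**Conclusion.** The point holds as a free improvement. The outcome wording and the model wording should agree, and baseline HOMA-IR should be named in the primary model. Following the model as named gives up precision and leaves chance baseline imbalance unadjusted.

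The gain is a rise in power from 80% to about 84%, 90% or 94% at rho 0.3, 0.5 or 0.6. Put differently, at rho 0.5 about 1185 subjects would do the work of 1580. These are upper figures. They rest on an assumed rho, a back-solved SD of about 1.0 taken as a single-time SD, a two-sided test, equal allocation, a common design effect, and no credit for the covariates already named. No bias and no failure to reach the stated 80% power is claimed.

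**What to change.** In Outcomes and in Data management and statistical analyses, state one dependent variable: HOMA-IR at one year. In the primary mixed model, with its household random intercept, name baseline HOMA-IR as a covariate alongside those listed. In Sample size, say which mean and which SD the 0.18 refers to.

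An alternative is a constrained longitudinal mixed model, with baseline and one-year HOMA-IR both as outcomes, a common baseline mean across arms, and random effects for household and subject. It must also include a household-by-time term: if changes correlate within households, leaving this out can make the standard error of the treatment effect too small. This model keeps participants lost after baseline, under a missing-at-random assumption. The covariate-adjusted model does not keep them, so the two are not interchangeable on dropout.

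Do the same for the continuous secondary outcomes: BMI, waist circumference, fasting and 2-hour glucose, HbA1c and lipids.

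The cost is analysis wording. The baseline measurements are already scheduled, and the Trial design section keeps the treatment codes closed until the data are cleaned and entered, so the change can be fixed before unblinding. The longitudinal option takes slightly more care to specify.

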### Ethical approval, trial registration and consent

This study has been approved by The Health Research Ethical Committee, Faculty of Medicine, Universitas Indonesia Cipto Mangunkusumo Hospital, Jakarta, Indonesia (reference number:549/H2.F1/ETIK/2013). It has also been filed by the ethics committee of Leiden University Medical Center and is registered as a clinical trial ref: ISRCTN75636394 (http://www.isrctn.com/ISRCTN75636394). The local health authorities have been informed about this study and have given their approval and support. The study, its benefits and risks are explained to the population and consent forms are distributed to be signed by the subjects who are willing to participate in this study. They are informed that they can withdraw from the study at any time, for any reasons and without any consequences.

### Description of the population recruited

So far, the study has provided the following data (Figure 1). At baseline, a total of 3698 individuals were registered in 752 households. Of the 2428 subjects aged 16 years or older, 1669 subjects were eligible with consent for examination. For the oral glucose tolerance test and immunological studies 339 subjects were randomly selected and gave approval.

**Figure 1 Fig1:**
[figure not shown]
**Flow diagram of the Sugarspin project.**

Figure 2 shows the age pyramid of both the total population in the study area and the study population. In the study population farming and fishing are the traditional source of income while some individuals engage in jobs at government offices or in the private sector (Figure 3), a similar distribution is seen in the total population. The education level of the majority of subjects in the study population is elementary school (33%), followed by senior high school (22%), and junior high school (16%), while 11% has college or university degrees. Moreover, 18% of the subjects is illiterate, either not educated at all or dropped out from elementary school (Figure 4). A similar distribution of the education level is seen in the total population.

**Figure 2 Fig2:**
[figure not shown]
**Age pyramid.** Age pyramid of all individuals living in the study area in Nangapanda, Flores Island, Indonesia (n = 3698 subjects, 52% female) **(A)**, and of study participants (n = 1669 subjects, 60% female) **(B)**.

**Figure 3 Fig3:**
[figure not shown]
**Job distribution.** At baseline, profession was assessed for study participants (n = 1669 subjects).

**Figure 4 Fig4:**
[figure not shown]
**Education level.** At baseline, education level was assessed for study participants (n = 1669 subjects).

## Discussion

The SUGARSPIN trial is the first and currently the only longitudinal study investigating the effects of anthelmintic treatment on whole-body insulin sensitivity. This placebo-controlled trial enables us for the first time to investigate the causal relationship between helminth infections, systemic inflammation and glucose metabolism in humans. In addition, this study will provide data on anthelmintic treatment efficacy and effectiveness in a large population in a developing country like Indonesia.

## Abbreviations

DM2: Type 2 diabetes mellitus
FCRC: Field clinical research center
OGTT: Oral glucose tolerance test
STH: Soil-transmitted helminth
Th2: T-helper-2
